## **Sample Size**

The sample size calculation was based on the main comparison, music intervention compared to standard care. The two primary outcomes are equally important.

The first primary outcome, change in brain age (Franke et al., 2010), is measured on an interval scale (months deviation from normal) over 12 months. To our knowledge, no previous studies have examined intervention effects on brain age. The second primary outcome, change in total depression symptoms, as measured by the BDI over 12 months, is also a continuous measure. A previous Cochrane review of music interventions for people with depression (van der Steen et al., 2017) found small to medium effect sizes on depression symptoms ( $d = 0.28$ ). However, this new music intervention will be different from previous interventions as it will be longer, have more frequent use music lessons, a daily intervention with home based practices and a choir. Singing in a choir also enhances the social aspect of the intervention. Furthermore, the study design will be different because it will be more focused on early stage AD, which possibly excludes some of the behavioural problems in previous studies. The current study will include a more homogeneous population by only including people with AD, not all types of dementia, which may also

differentiate the findings somewhat. Finally, the main comparison in this study is music intervention versus standard care, whereas the meta-analyses in the Cochrane review included a mix of comparisons with standard care and active controls. Therefore, a medium-to-large effect size (between 0.50 and 0.80) may be realistic to expect for the current study. With an assumed medium-to-large effect size of  $d = 0.7$ , a t-test with a two-sided significance level of 2.5% will reach 80% power with 40 participants in each group. To account for possible attrition, we will aim to recruit at least 45 participants per group, for a total target sample of 135 participants across the three groups. This is seen as a minimum number, so that we will not dismiss participants if we exceed the number of 45 participants in each group.

## **Recruitment**

Participants will be recruited through media announcements and planned visits to day centres in Bergen and the areas around. We have contacted the general medical practitioners organization and informed them about the study and they have put it into their website for doctors to read if patients ask about treatment. We have also printed and distributed our flyer with the home assistants and other therapists and day centers where the patients might go.

## **Randomisation and Allocation Concealment**

Block randomisation with randomly varying block sizes of 3 or 6 will be used to ensure balance as well as unpredictability. The randomisation list will be computer-generated and kept concealed by a researcher who has no direct contact with the participants ([name] at Uni Research). The randomisation result will be revealed to the clinical investigators only after inclusion has been confirmed (eligibility confirmed, informed consent signed, baseline testing completed). Participants will be identified through an ID number and basic demographics (age, sex, diagnostic code), and the randomisation result will be communicated in written electronic form (using university email or a dedicated server for clinical trial data).

## **Blinding**

Blinding of participants: Before randomisation, participants will be informed of the three different interventions they may be offered (of which one is no intervention). Due to the nature of the interventions, it will not be possible to blind participants to the intervention received.

Blinding of outcome assessors: Assessment of brain imaging data (including the first primary outcome) will be blinded by ensuring that the data analyst is unaware of the intervention received. The self-report measures (including the second primary outcome) cannot be blinded. The PhD students who will be responsible for data collection and interventions will not be involved in the data analysis.

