### **Trial Design**

This is a parallel, three-arm, single-blind (assessor-blinded) randomised controlled trial. Participants will be randomised to either a music intervention (singing lessons), a non-musical training intervention or no intervention. To ensure allocation concealment, the randomisation list will be created and kept at an external research office at Uni Research, by researchers who have no direct involvement with the clinical work.

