exercise and no intervention. Although the study will randomise participants, it will indicate why some choose to drop out. The hope is that all participants who are recruited will get enough insight into the study to know that singing lessons, exercise or nothing are the options for participating in the experiment.

The biggest challenge is the control group that will not get any intervention. For the current study, participants are not to be medicated by us, but singing and exercise can be considered a kind of treatment, while the control group is not receiving any treatment. Regular medical treatment that patients usually use is acceptable and they will continue with it during the trial period. That is, the participants get the best beneficial treatment as established in medical research. Music and exercise are two of the best options for non-medical treatment, therefore all groups will receive good treatment. As mentioned in the background section, music and exercise are two of the best options for non-medical treatment, therefore all groups will receive good treatment.

For the current project, co-authorship might become problematic. As there will be three PhD positions on the project, they will all want to be first author on the publications. There are also a limit to how many articles one project can yield. Also as the project has many partners, there might be difficult to detect when which authors should be mentioned in articles or not.

As the project cooperates with Bergen municipality positive findings will be implemented into the health care system. Betterment of health care is a positive implication of the possible findings. However, new music treatment which works may demote other research of being implemented, or research to be done in the field at all. For music may be good medication, it might not be a cure for AD. Also because this is a massive study, which takes time and money, others may not replicate it. Which is why the societal implications of the findings might be negative as well as positive.

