### 3. ADL

“Oki, supert. Nå skal jeg spørre deg litt om hva du gjør i hverdagen,”

*Still spørsmålene og se om svaret passer i noen av boksene, hvis ikke kan du grave litt for å få et alternativ som passer i boksene. Gå tilbake og bruk ordliste to for gjenkjennelse og gjenkallelse.*

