### 4. GDS

“Kjempe bra. Nå skal jeg spørre deg litt om humøret ditt og hvordan du føler deg til vanlig. Jeg vil at du skal fylle ut denne listen,”

*Gi deltakeren GDS og la de svare selv, med blyant som de allerede har. Hjelp ved behov.*

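### The trial is labelled assessor-blinded, but only the imaging analysis is blinded; 12-month outcomes that depend on the tester are not

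*Protocol*

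**What the plan says.** The Trial Design section describes a "parallel, three-arm, single-blind (assessor-blinded) randomised controlled trial".

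The Blinding section, under outcome assessors, makes three statements:
- On imaging, it says that the assessment "will be blinded by ensuring that the data analyst is unaware of the intervention received". This covers brain age.
- On questionnaires that participants fill in, it concedes that blinding is impossible, and it counts the GDS among them.
- On staffing, its only safeguard is this: "The PhD students who will be responsible for data collection and interventions will not be involved in the data analysis".

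Randomisation and Allocation Concealment has the allocation disclosed to the clinical investigators once baseline testing is complete. Data management gives the data collectors, and nobody else, access to the code keys and patient information.

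Appendix D is the only testing script. For the GDS the tester is to "la de svare selv, med blyant som de allerede har. Hjelp ved behov" (let participants answer themselves, help as needed). For the ADL interview the tester is told to "Still spørsmålene og se om svaret passer i noen av boksene, hvis ikke kan du grave litt" (ask, see whether the answer fits a box, and otherwise dig a little). The tester also conducts the MMSE and writes down how many words are recalled.

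**The concern.** The label promises that whoever measures the outcome does not know the arm. The Blinding section delivers this for one role, the imaging analyst. Its account covers imaging and self-report. It is silent on a third class, the tests that a tester administers and scores, where blinding is feasible. In their place it offers only a separation between data collection and analysis, which guards against a different bias.

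The comparison at stake is music versus standard care, which Statistical Methods names as primary. The Outcomes section states the direction expected for depression: lower after music or exercise, unchanged in the control group. A tester who is responsible for the interventions and knows the arm can influence the 12-month score through encouragement, probing, or help with an item, without intending to. A reader who relies on the label would give the behavioural results more weight than the design supports.

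**Working it through.** **1. Who produces each 12-month score, and is that role blinded?** (Secondary Outcomes, Blinding, Appendix D)

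| Outcome | How the score arises | Blinding at 12 months |
|---|---|---|
| Brain age (primary) | Imaging analyst | Yes |
| GDS (primary) | Participant, with tester help if needed | Open, conceded; tester help not addressed |
| ADL | Tester asks, probes and chooses the box | None provided |
| MMSE | Tester administers | None provided |
| Word learning | Tester counts recalled words | None provided |
| Stroop | Computer scores; tester explains | None provided, but less exposed |
| Finger tapping | Run on a computer | None provided, but less exposed |

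**2. When can knowledge of allocation act?** The behavioural tests are given before randomisation and after 12 months, and allocation is disclosed only after baseline. So only the 12-month value, and through it the change score, can be affected.

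**3. The protocol's own sample size** (d = 0.7, two-sided 2.5%, 80% power, 40 per group). Normal approximation: 2 × (2.2414 + 0.8416)² / 0.7² = 2 × 9.505 / 0.49 = 38.8, so 39 per group. The exact two-sample t-test gives 40.08 per group, and 79.9% power at 40. The stated figure reproduces and is not in dispute.

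**4. Illustration of scale.** The protocol gives no size for detection bias, so the values below are assumptions.

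Smallest significant difference with 40 per group:
- Primary level, 2.5%: t(0.9875; 78 df) × √(2/40) = 2.2855 × 0.2236 = 0.511 SD.
- Secondary level, 5%: t(0.975; 78 df) × √(2/40) = 1.9908 × 0.2236 = 0.445 SD.

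A bias of 0.2 SD would be 0.2/0.511 = 39% of the first and 0.2/0.445 = 45% of the second.

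Chance of a significant result with no true effect, from the noncentral t distribution, 40 per group:

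| Assumed bias (SD) | GDS, 2.5% level | A tester-scored secondary outcome, 5% level |
|---|---|---|
| 0 | 2.5% | 5.0% |
| 0.1 | 3.9% | 7.3% |
| 0.2 | 8.8% | 14.3% |
| 0.3 | 17.9% | 26.3% |
| 0.4 | 31.5% | 42.4% |

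The GDS column does not measure what a blinded tester would gain. Participants know their arm, so most expectation bias on a self-report scale would remain. Only the part due to tester help is avoidable.

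**The case against.** Much of the case on the other side stands.

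- **Delivery by the testers.** A reader might infer that the PhD students treat participants for a year and then test them, so that participants answer to please their own therapist. The protocol does not say this. The Blinding section says the students are responsible for the interventions. Trial Design and Rationale names vocal teachers, conductors, music therapists, physiotherapists and occupational therapists as performing them, and the Interventions section allows advanced students under supervision without saying who these are. The concern rests on likely knowledge of allocation, not on a therapeutic relationship.
- **Appendix D.** The script opens with consent and includes the background questionnaire, SPPB and PROMS, which are scheduled only before randomisation. It therefore reads as the baseline visit, when allocation does not yet exist for that participant. Its latitude matters only if the same instructions are used at 12 months. That is plausible, since the GDS, ADL and cognitive tests are repeated and no other script is given, but it is an inference.
- **All cognitive tests exposed.** This would be too broad. Stroop is scored digitally and finger tapping is run on a computer. The tester's explanation and encouragement remain, but not the scoring.
- **GDS.** The protocol discloses that it is open, and participants complete it themselves. What is not addressed is the undefined help.
- **Weight.** Brain age is read blind, and the tester-scored outcomes are secondary and exploratory.

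None of this restores the label. No section arranges a 12-month tester unaware of allocation, and nothing keeps those responsible for both tasks from knowing it.

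**Conclusion.** The stated blinding is broader than the design. Only the imaging analysis is blinded. The 12-month MMSE, word learning test, ADL interview and any tester help with the GDS are open to detection bias in music versus standard care. This rests on two readings: that the people responsible for both data collection and interventions will know allocation by 12 months, and that the Appendix D instructions are reused then.

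The size of the bias cannot be estimated from the document. The 0.1 to 0.4 SD range shows sensitivity and is not a forecast. The point should be corrected because the label is inaccurate and the remedy is mostly wording. It does not undermine the brain-age outcome, and it does not show that participants are tested by their own therapist.

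**What to change.** 1. **Correct the claim.** In Trial Design and Blinding, state that only the imaging analysis is blinded, that the GDS is self-reported and open, and that the other behavioural tests are not assessor-blinded unless step 3 is adopted. This costs wording and a narrower blinding claim.
2. **Script the tester.** In Appendix D, limit GDS help and ADL probing at both visits to fixed neutral prompts, such as reading items aloud. This costs a short script.
3. **Separate the roles where existing staff allow.** Have each 12-month session run by a team member with no part in that participant's intervention. Withhold allocation and the code key from that person, ask participants not to reveal their group, and record any unblinding.

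Step 3 needs changes to Randomisation and Allocation Concealment and to Data management. Ethical Challenges mentions three PhD positions ("As there will be three PhD positions on the project"), but in a passage on authorship that does not say how the work divides. A rota among those students would not by itself conceal allocation while data collectors hold the code keys. The cost is less flexible booking of test sessions. If no existing team member can be kept unaware of allocation, steps 1 and 2 still apply.

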## **Data management**

All health information will be treated with the utmost confidentiality. Participants anonymity will be secured by the code key for each participant. The code keys and patient information will be locked in the office of the project manager, in two separate cabinets. Only the data collectors will have access.

Data will be stored on computers, but they will be anonymised with the code key for each participants. They will be plottet directly into spreadsheets in Excel and SPSS from paper form and computer outputs.

## **Treatment of Human Biological Material**

Not relevant to the current project.

## **Statistical Methods**

All primary analysis will be conducted in the modified intention-to-treat population, i.e. all who were randomised and for whom outcome data are available will be analysed in the group to which they were randomised, regardless of whether they received the full intended intervention. All continuous variables will be screened for normality of distributions. If normality is confirmed, the three interventions will be tested in an overall test (one-way ANOVA with three levels), followed by multiplicity-adjusted post-hoc t-tests (as described in Statistical analyses below). However, only one comparison – music intervention versus standard care – is regarded as the primary comparison. Multiplicity adjustment is made for the two primary outcomes, leading to a two-sided 2.5% significance level. All other comparisons and outcomes are regarded as exploratory secondary and are not multiplicity-adjusted (i.e. will be tested on a two-sided 5% level). Additional sensitivity analyses will be conducted on the per-protocol population (by treatment received). Subgroups such as gender, education will also be investigated. Adjusted measures will be music aptitude at baseline. Working alliance will be examined as a mediator variable of later clinical outcomes.

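### The primary test is described inconsistently: a three-arm ANOVA with adjusted post-hoc tests in one sentence, a single direct 2.5% t-test in the sentences that follow and in the power calculation

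*Protocol*

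**What the plan says.** Protocol, Statistical Methods, gives two descriptions in one paragraph. If normality is confirmed, the three interventions are to be "tested in an overall test (one-way ANOVA with three levels), followed by multiplicity-adjusted post-hoc t-tests", with a pointer to a section on statistical analyses further down. No later section of that name appears in the protocol.

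The paragraph then turns with a contrasting word. Only music versus standard care "is regarded as the primary comparison". "Multiplicity adjustment is made for the two primary outcomes, leading to a two-sided 2.5% significance level". And: "All other comparisons and outcomes are regarded as exploratory secondary and are not multiplicity-adjusted", with a two-sided 5% level given for these.

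Protocol, Sample Size, takes the second line: "The sample size calculation was based on the main comparison, music intervention compared to standard care". With d = 0.7, "a t-test with a two-sided significance level of 2.5% will reach 80% power with 40 participants in each group". For attrition, "we will aim to recruit at least 45 participants per group, for a total target sample of 135 participants across the three groups". That calculation includes neither an overall test nor an adjustment across pairs of arms.

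**The concern.** The t-tests that follow a three-level ANOVA are the pairwise comparisons of the arms. They cannot be multiplicity-adjusted in one sentence and, apart from the primary one, unadjusted a few sentences later. An overall test followed by post-hoc tests is also the usual wording for a gated sequence, in which the pairwise tests count only if the ANOVA is significant. On that reading the exercise arm, which is not part of the primary comparison, helps decide whether the primary comparison may be claimed.

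A music effect significant at 2.5% could then be reported as positive by one analyst and negative by another, each following the text in good faith. This applies to both primary outcomes, which the protocol calls equally important. The overall test is not needed for error control here: there is one pre-specified contrast per outcome, and the 2.5% level already covers the two outcomes.

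**Working it through.** **Inputs.** From Sample Size: n = 40 per arm analysed, 45 recruited, d = 0.7, two-sided α = 0.025, power 80%. Allocation is 1:1:1 (equal group targets, blocks of 3 or 6). The primary-outcome text expects exercise to reduce depression too but gives no size, so the exercise mean is varied from 0 to 0.7 SD above control. The ANOVA level is not stated, so 5% and 2.5% are both tried. Normal data and equal variances are assumed.

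**Step 1: reproduce the stated power.** For a two-sample t-test, df = 2n − 2 = 78 and the noncentrality is d√(n/2) = 0.7 × √20 = 3.130. The two-sided 2.5% critical value is 2.285. The noncentral t distribution gives power 79.9% at n = 40 and 84.9% at n = 45. The plan's figure is reproduced.

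**Step 2: what a gate would demand.** With n per arm, pooled variance MSE and observed music-minus-control difference δ, t² = nδ²/(2·MSE) and F = n·s²/MSE, where s² is the sample variance of the three arm means.
- Exercise midway (means δ, δ/2, 0): s² = δ²/4, so F = t²/2.
- Exercise equal to music or to control: s² = δ²/3, so F = (2/3)t².

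The critical values of F on 2 and 117 df are 3.07 (5%) and 3.81 (2.5%). The gate therefore needs:
- midway: |t| > √(2 × 3.07) = 2.48 at 5%, or √(2 × 3.81) = 2.76 at 2.5%;
- equal to one arm: |t| > √(1.5 × 3.07) = 2.15 at 5%, or √(1.5 × 3.81) = 2.39 at 2.5%.

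The direct test needs about 2.29. A 5% gate thus costs little, while a 2.5% gate with exercise midway is a clearly higher hurdle than the one that was powered.

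**Step 3: power by reading.** Simulation with true means 0.7 / x / 0 (music / exercise / control), SD 1, 400,000 replicates per scenario; the direct-test and no-gate Bonferroni rows are exact:

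| Reading | n = 40 | n = 45 |
|---|---|---|
| Direct t-test at 2.5% | 79.9% | 84.9% |
| ANOVA gate at 5%, then t at 2.5% | 77.0–79.2% | 82.3–84.4% |
| ANOVA gate at 2.5%, then t at 2.5% | 69.6–76.4% | 75.8–82.2% |
| ANOVA gate at 2.5%, then Tukey at 2.5% | 67.0–68.3% | 73.5–74.8% |
| Bonferroni over three pairs (0.025/3), no gate | 66.4% | 73.1% |
| ANOVA gate at 2.5%, then Bonferroni over three pairs | 65.0–66.1% | 71.9–72.9% |

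In each range the low end is exercise midway (0.35 SD) and the high end is exercise equal to control or to music. With the three-pair Bonferroni level and no gate, 52 per arm would be needed for 80%.

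**Step 4: the optional Holm step.** At n = 40 and d = 0.7 on both outcomes, single-test power is 0.799 at 2.5% and 0.871 at 5%. If the outcomes are independent, Holm power per outcome is 0.799 + (0.871 − 0.799) × 0.799 = 0.857. The chance of success on both rises from 0.799² = 0.64 to 0.871² − (0.871 − 0.799)² = 0.75.

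**The case against.** The strongest reply is that the paragraph resolves itself. It states an order of tests but never says that the t-test depends on a significant ANOVA. The contrasting sentence then singles out one primary comparison, and the next defines the adjustment as the one across two outcomes, which matches the Sample Size section exactly. The cross-reference may simply mean the sentences that follow: Eligibility Criteria uses the same title for the intention-to-treat rule, and that rule is found in Statistical Methods. On this reading the plan is coherent and has its 80%.

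Much of this stands. A reader might infer that the stated power is not delivered. The documents do not support that as a fact: a binding gate is implied at most, a 5% gate costs only about 1–3 points, and the 65–66% figure needs a pairwise Bonferroni adjustment that the protocol nowhere mentions. A reader might also take the equal 2.5% split across outcomes for a mistake because Holm is more powerful. The split is valid and is what the power calculation used.

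What does not stand is that a favourable reading makes the rule specified. The adjusted post-hoc wording still contradicts the later statement that other comparisons are unadjusted. The contrasting sentence can be read as replacing the sequence or merely as labelling one of its contrasts. This goes beyond detail that an analysis plan could supply, because the protocol itself fixes two incompatible descriptions.

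**Conclusion.** The concern holds as an inconsistency in the primary decision rule, with a loss of power that depends on the reading. The sample size calculation is correct, and under a direct test its 80% is delivered. Relative to 79.9% at n = 40, the loss is about 1–3 points with a 5% gate, about 4–10 points with a 2.5% gate, and about 12–15 points if the primary contrast is also adjusted across pairs (Tukey or Bonferroni).

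These sizes rest on d = 0.7, normal data with equal variances, an assumed exercise effect between 0 and 0.7 SD, and assumed ANOVA levels. If all 45 recruited per arm were analysed, a 5% gate would still leave more than 80%, but a 2.5% gate with exercise midway would not (75.8%). The larger stake is that the choice between readings could otherwise be made after the data are seen.

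**What to change.** In Statistical Methods:
- State that for each primary outcome music versus standard care is tested directly at two-sided 2.5%, regardless of the ANOVA result.
- Delete the wording on multiplicity-adjusted post-hoc tests, so that music versus exercise and exercise versus control are plainly exploratory and unadjusted at 5%, as the paragraph already says.
- Keep the three-arm ANOVA, if wanted, as a secondary or descriptive analysis.
- Correct the cross-reference, here and in Eligibility Criteria, so that it names a section that exists.

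If the sponsor does intend a gate, its level must be given and the power restated for that gate alone: 77.0–79.2% at 5% or 69.6–76.4% at 2.5%, at 40 per arm. The 65–66% figure belongs to an added pairwise adjustment and should not be attributed to the gate.

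As an optional gain, and not as the correction of an error, Holm could be used across the two primary outcomes: the smaller p-value at 2.5% and, if significant, the other at 5%.

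The cost is wording only. Sample size, data collection and the primary comparison stay as they are. The change should be made before database lock.

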### **Eligibility Criteria**

All adults with AD, above the age of 18, of any gender, are eligible to participate. In addition to having a diagnosis of AD, participants must live at home (not in a residential aged care facility, however they may have plans to move to such a facility in the future) and be able to give informed consent for the study. They also need to be able to complete questionnaires in Norwegian, to undergo magnetic resonance scans, and to attend intervention and assessment sessions in the area of Bergen, Norway. Participants can be non-musicians, amateur/hobby musicians, or professional musicians.

If participants move to a nursing home during the intervention period, they will not be excluded. All participants randomised will be retained and analysed, according to the intention-to-treat principle (see Statistical analyses).

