## **Control Intervention**

The control group will continue on medications and activities that they usually have. They will not be asked to quit training or music if they are currently participating in such activities.

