## **Assessment of Attendance and Fidelity**

Participation in the program will be documented by the therapists in charge of the intervention by simply marking if the participants attend the intervention. 80 % participation is required for inclusion in analysis.

Mid intervention we will also interview participants about how they like their therapist and the therapy, and if they are doing the interventions on their own at home. However, there will be no strict measures of whether they do the intervention on their own. This is encouraged, but not a must.

There will be a midway evaluation of therapists for both the active interventions. Here we will inquire if they overlapped in any way. Both will be asked the same questions:

«Did you use music?», «Did you use exercise?»

Then we will ask the participants the same questions about the therapy sessions. This includes double self-reports from therapists and participants. In addition we will ask participants for their compliance, or how much they practiced on their own.

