## Ethics and Dissemination

### **Ethical Challenges**

The current study is investigating an exposed group, people who have Alzheimer's disease. Even at an early stage in the disease, this group may be considered exposed. For the current study it is important that participants are living at home and the interventions may help them stay home longer. Music and exercise have the health and positive effects on patients with AD, but also generally older people and their caregivers. Nevertheless, there is little high quality research on long-term music and exercise therapy in people with AD. Therefore, this study holds great potential; it is an exploratory study. Little suggests negative effects of song and exercise in people with AD. The literature states that depression and anxiety decreases with music therapy, and well-being increases, but no evidence suggests a stop of disease progression.

The group may not continue to stay home during the intervention, the literature states that depression, anxiety decreases with music therapy, and well-being increases, but it is no evidence that suggests a stop of disease progression. We assume new learning and active use of hippocampus may have positive effects on the brain. If participants move away from home during the period, they will continue to receive the same offers from us. We expect some dropouts from the study, hence we want to test as many patients as possible. If participants no longer wish to do the intervention, but still want to be tested, that will be allowed. If participants wish to do the intervention, but not be tested they will be allowed to do that as well.

fMRI and MR may be experienced as uncomfortable by some participants, but are necessary for the research, however it is not dangerous for the participants.

Retrieval of personal data and neuropsychological tests can also be uncomfortable for some of the participants, but where a computer can be utilized, it will, to limit researcher access and vulnerability of participants.

Music therapy or exercise may not be attractive to everyone. Song has ecological validity in our everyday lives. We humans often meet and sing in different contexts, such as for weddings, funerals, in church, at work and school. We will also ask participants what they prefer of singing,

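### The supporting analysis joins two different analyses, per-protocol and by treatment received; neither keeps the randomised comparison, and either can mislead if stopping is related to outcome

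*Protocol*

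**What the plan says.** Statistical Methods makes a modified intention-to-treat analysis primary: "all who were randomised and for whom outcome data are available will be analysed in the group to which they were randomised", whether or not they received the full intervention. The same section then adds: "Additional sensitivity analyses will be conducted on the per-protocol population (by treatment received". It does not define that population further.

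The only adherence rule is under Assessment of Attendance and Fidelity: "80 % participation is required for inclusion in analysis". It is not tied to any named analysis set. The attendance record comes from the active arms: "Participation in the program will be documented by the therapists in charge of the intervention".

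Three other statements bear on the point:

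- Eligibility Criteria: "All participants randomised will be retained and analysed, according to the intention-to-treat principle".
- Ethical Challenges, on people who stop: "If participants no longer wish to do the intervention, but still want to be tested, that will be allowed".
- Control Intervention, on controls: "They will not be asked to quit training or music if they are currently participating in such activities".

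**The concern.** A per-protocol analysis and a treatment-received analysis handle the same person differently. Take a music participant who stops singing but attends the 12-month tests, which the protocol permits. Per-protocol leaves that person out. A treatment-received analysis keeps that person and, since what was received is close to usual care, counts the outcome with the controls. The sentence names one analysis and glosses it as the other, so the analyst has to choose.

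Both choices compare groups that randomisation did not form. The selection is also one-sided: a control cannot miss sessions that were never offered, so attendance sorts the music arm and leaves the control arm whole. If those who stop are those who are declining, their poorer outcomes leave the music mean and, by treatment received, enter the control mean.

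At stake is how the supporting result is read. Called a sensitivity analysis, a favourable result would be taken as confirming the primary one, although it does not test the primary analysis's own assumptions, such as those about missing outcomes.

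**Working it through.** **The plan's own figure.** Sample Size gives 40 per group for d = 0.7, two-sided 2.5% and 80% power. This reproduces: the normal approximation gives 39, the t-test gives 40.08, and power at 40 is 79.9%. So 40 per arm and the 2.5% level are used below.

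**Inputs not in the protocol (assumed).** q is the share of the music arm that stops, 20-30%. δ is how much worse stoppers' outcomes are than adherers', 0.5-1.0 SD. SD is the spread within each of those two types of participant. There is no true effect, both arms contain the same mixture of types, and everyone is tested.

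**Formulas.** Set the overall mean to 0. Adherers then have mean qδ and stoppers −(1−q)δ.

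- As randomised: 0 − 0 = 0.
- Per-protocol (music stoppers dropped, all controls kept): qδ − 0 = qδ.
- By treatment received (music stoppers added to the controls): the enlarged control group has mean −q(1−q)δ/(1+q). The difference is qδ + q(1−q)δ/(1+q) = 2qδ/(1+q).

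The false-positive rates are from 6,000 simulated trials per setting.

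| q | δ | Per-protocol bias (SD) | By treatment received (SD) | False positives, per-protocol | False positives, by treatment received |
|---|---|---|---|---|---|
| 0.2 | 0.5 | 0.10 | 0.20/1.2 = 0.17 | 3.9% | 6.4% |
| 0.3 | 0.5 | 0.15 | 0.30/1.3 = 0.23 | 5.5% | 9.5% |
| 0.2 | 1.0 | 0.20 | 0.40/1.2 = 0.33 | 7.5% | 17.9% |
| 0.3 | 1.0 | 0.30 | 0.60/1.3 = 0.46 | 13.1% | 31.3% |

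The as-randomised test stays at 2.3-2.8% throughout, against a nominal 2.5%.

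**A different selection model.** Let stopping depend on a latent factor with correlation r to improvement, with 80% compliance and no true effect:

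- r = 0.3: bias +0.105 SD per-protocol and +0.175 SD by treatment received; rejection 4.0% and 7.0%, against 2.4% as randomised.
- r = 0.5: bias +0.175 and +0.29 SD; rejection 6.3% and 15.0%.
- r = 0: no bias.
- r = −0.3: the bias reverses, −0.11 and −0.18 SD.

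**A smaller stopping share.** The only loss figure in the protocol is the allowance from 45 to 40 per group, 5/45 = 11%. It concerns attrition, not stopping, but it gives a lower reference point. With q = 1/9 and δ = 0.5, per-protocol bias is 0.5/9 = 0.06 SD. By treatment received it is (2 × 0.5/9)/(10/9) = 0.10 SD.

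**The complier-average estimate.** This is the as-randomised difference divided by the compliance share. With no true effect it is about 0 in every setting of the second model. It is not assumption-free. Take an effect of 0.7 in compliers and 80% compliance:

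- If stoppers get nothing: (0.8 × 0.7)/0.8 = 0.70, which is correct.
- If stoppers get half the effect: (0.8 × 0.7 + 0.2 × 0.35)/0.8 = 0.63/0.8 = 0.79, which is too large.

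**The case against.** The strongest reply is that the sentence names a single population. The bracketed words may mean only those who received their allocated treatment, in contrast to the primary set, which is analysed regardless of receipt. On that reading nobody is moved to the control arm and the treatment-received figures do not apply. This stands: the phrase is ambiguous and undefined, and a reader who infers that stoppers will certainly be counted as controls goes beyond the text. The per-protocol figures remain, because that reading also selects on adherence in the active arms alone.

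A reader might also infer that the analysis is biased towards music. The protocol does not support that. It does not say who stops, and the reason for dropout that it raises is preference: Other Measures and Ethical Challenges ask which arm people would prefer as a clue to why some leave. Stopping for reasons unrelated to outcome produces no bias.

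The analysis is additional, with no confirmatory role, so it cannot formally rescue a null primary result. That also stands. The exact definition of a per-protocol set is commonly left to the SAP. The issue here is not a missing definition but a stated gloss that points to a different analysis.

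Finally, a complier-average estimate does not simply remove the problem. It needs extra assumptions, tests the same null as the as-randomised analysis and adds no power. It therefore belongs beside a properly defined per-protocol analysis; replacing that analysis outright would be a preference.

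**Conclusion.** The point holds as a defect in the supporting analysis. The wording merges dropping non-adherers with regrouping them, and neither keeps the randomised comparison. With no true effect and the assumed 20-30% stopping and 0.5-1.0 SD deficit, the spurious benefit is 0.10-0.30 SD per-protocol and 0.17-0.46 SD by treatment received, against a planned effect of 0.7. Both the direction and the size depend on those assumptions.

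The point does not extend to the primary analysis as Statistical Methods defines it. The 80% rule is a related matter: as worded it requires attendance for any analysis, which conflicts with the intention-to-treat statements in Eligibility Criteria and Statistical Methods. Confining it to the per-protocol set settles both.

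**What to change.** In Statistical Methods:

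1. Delete the bracketed words after the per-protocol population.
2. Define that population by the 80% attendance rule. State that the rule applies to this set only, not to the primary analysis, and that participants stay in their randomised arm. Amend the sentence under Assessment of Attendance and Fidelity to match.
3. Call the analysis supplementary. Keep the term sensitivity analysis for departures from the primary analysis's assumptions.
4. Add a complier-average estimate, with randomisation as instrument and recorded attendance, at the same threshold, as exposure.
5. State its assumptions: attendance below the threshold has no effect; how receipt is defined for controls who already do music; and outcomes are obtained from those who stop. Missing 12-month outcomes would bias this estimate too.

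The cost is a wording change and one extra model on attendance that is already recorded. The downside is a wider interval than the per-protocol estimate and reliance on the exclusion restriction.
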